## *Summary*

Chronic pelvic pain (CPP) affects >1 million UK women. Annual healthcare costs are estimated at >£150 million. Proven interventions for CPP are limited and treatment is often unsatisfactory. Gabapentin is increasingly prescribed due to reports of effectiveness in other chronic pain conditions, but there are insufficient data supporting value in CPP specifically. The mechanism of action of gabapentin in CPP is also unclear. Given the prevalence and costs of CPP, we believe a large multi-centre placebo-controlled double-blind randomised-controlled trial (RCT) to evaluate the efficacy of gabapentin in management of CPP is required along with exploration of its mechanism of action. The focus of this study is a pilot to inform planning of a future RCT. We aim to recruit 60 women with CPP in NHS Lothian and NHS Grampian and randomise them to gabapentin or placebo. Response to treatment will be monitored by questionnaire at 3 and 6 months. A random subset of 24 Edinburgh women will undergo functional magnetic resonance imaging of the brain at 3 months. Our primary objective is to assess recruitment and retention rates and to obtain data to refine the research methodology for the RCT. We also aim to perform a pre-trial cost-effectiveness assessment of treatment with gabapentin.

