### 7.2 STUDY ASSESSMENTS

(See Appendix 5 for additional detail)

Baseline (0 months): **Visit 1**

Informed consent

Screening

Eligibility confirmed

Randomisation to gabapentin or placebo

Treatment diary

Questionnaire

Week 1 Telephone interview

Week 2 Telephone interview (if dose escalation not finished)

Week 3 Telephone interview (if dose escalation not finished)

Week 4 Telephone interview (if dose escalation not finished)

Week 5 Telephone interview (if dose escalation not finished)

Week 6 (+/- 7 days) **Visit 2**

Short interview

Dispensing of drugs if necessary

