### 3 months (+/- 7 days) **Visit 3**

Questionnaire  
Dispensing of drugs if necessary  
Brain fMRI (Edinburgh subset)

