### 6 months(+/- 7 days) **Visit 4**

Questionnaire  
Unblinding  
Collection of treatment diary  
Collection of any unused study medications

3 - 6 months              Focus groups (subset)

The following measures will be completed by the subject in a daily treatment diary beginning on Day 1 of treatment.

- Time and dose of gabapentin taken
- Reason for any change in trial medication dose
- Concomitant medications taken
- Alternative therapies used
- Any visits to a healthcare professional
- Adverse events
- Weekly average Lickert pain score

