### **fMRI**

24 participants in Edinburgh will be allocated to undergo functional magnetic resonance imaging (fMRI) of the brain at 3 months (as long as they satisfy safety issues related to the procedure). The study of fMRI requires the need to contrast periods of brain activation (induced by pain) with periods of rest. Therefore, subjects will be asked to lie still and a weighted ball will be applied to the abdomen at regular intervals during the procedure (block design with alternating periods of 16 seconds of 'pain' and 16 seconds of 'rest') (Liu et al, 2001). Pain levels will vary per subjects so we will include a 'rating scale' to allow us to do a regression analysis of fMRI level of activation as a function of the level of pain. Pain levels also vary according to the woman's menstrual cycle (reference). We will carry out the fMRI at the same stage of each participant's cycle. We will take a blood sample to measure hormone levels. Each fMRI will last ~30 mins: structural scans T1 and T2 (~10 mins), fMRI scan 16 seconds on/off repeated 20 times (~10 mins) and time for subject to get into and out of scanner and apply weighted ball in position (~10 mins). Discontinuation rules in case of patient distress will be as follows. Before the fMRI, we will assess the level of discomfort associated with the 'ball test' (plus obtain the 'rating'). We will also use a thermal resistor to deliver noxious thermal stimulation of a pre-determined intensity (the temperature adjusted for each subject to produce a rating of this intensity) as has been successfully used previously (VINCENT K, et al. Pain 2011 152(9):1966-75). Participants will also be given the opportunity to withdraw from this component of the study pre-fMRI. In addition, in the scanners, there is a button that participant can press to stop the scan. This will allow participants to withdraw from this component of the study during the fMRI. The fMRI studies will be performed in Edinburgh (3T Siemens MRI), supported by the Scottish Imaging Network, SINAPSE. We will calibrate the fMRI protocols by asking up to 4 healthy volunteers to undergo this procedure. They will complete a CRIC consent and safety form before taking part.

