#### (ii) Effectiveness and acceptability of proposed methods of recruitment, randomisation, drug treatments, questionnaires, use of brain fMRI and follow-up?

These areas will be explored in the focus group discussions and assessed quantitatively using additional questions included in participant questionnaires administered at 6 months. Due to the conflicting literature about the benefits of methods such as prescription monitoring, pill counting and devices for monitoring the self-administration of medicines (Melnikow and Kiefe, 1994), data on blinding and compliance to treatment will be derived from questionnaires at 6 months. We aim to determine if treatment is acceptable in terms of self-reported compliance (from treatment diaries). Although this is a pilot study and the sample size is small, we will assess the effect of any non-compliance on the LICKERT score by performing protocol and intention to treat analyses. This information along with health professionals' and clinical research nurses' views (as assessed by questionnaire) will be used to inform the design of the future RCT. (iii) Sensitivity of brain fMRI to study the effect of gabapentin in the management of CPP

The fMRI data will be analysed using a voxelwise approach and hierarchical linear modelling. An ANOVA [pre/post treatment\*gabapentin/ placebo] will be performed to investigate which areas of the brain gabapentin acts on compared to placebo. A regression analysis between brain activity and the behavioural measures will also be performed to evaluate the relationship between gabapentin brain activity and pain reduction. The brain fMRI scan results will then be compared with other studies of gabapentin (Iannetti 2005, Governo 2008) to determine the sensitivity of this approach to study the mechanism of action of gabapentin in CPP. We will use published fMRI methodology (Mumford & Nichols 2008) informed by the pilot to power future fMRI studies.

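### The planned fMRI test is a pre/post-by-arm ANOVA, but the text schedules only one scan, at 3 months on treatment, so that test cannot be run as written

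*Protocol*

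**What the plan says.** Section 9.2(iii) sets the test: "The fMRI data will be analysed using a voxelwise approach and hierarchical linear modelling. An ANOVA [pre/post treatment", crossed with gabapentin/placebo. It "will be performed to investigate which areas of the brain gabapentin acts on compared to placebo". The same paragraph adds a regression of brain activity on behavioural measures, a comparison with other gabapentin imaging studies, and use of the pilot to power later fMRI work.

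The scan is timed in three places:
- Summary: "A random subset of 24 Edinburgh women will undergo functional magnetic resonance imaging of the brain at 3 months".
- fMRI text under section 7.2: "24 participants in Edinburgh will be allocated to undergo functional magnetic resonance imaging (fMRI) of the brain at 3 months".
- Visit schedule in section 7.2: "Brain fMRI (Edinburgh subset") appears under Visit 3, at 3 months.

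The entry headed "Baseline (0 months): Visit 1" lists consent, screening, eligibility, randomisation, diary and questionnaire, but no scan. Visit 2 (week 6) lists an interview and dispensing. Visit 4 (6 months) lists a questionnaire, unblinding and returns, down to "Collection of any unused study medications", again with no scan. Section 3 gives six months of treatment after randomisation, so a scan at 3 months is taken on treatment.

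**The concern.** A pre/post-by-arm ANOVA answers its question through the interaction: does activation change more on gabapentin than on placebo? That needs at least one scan before treatment and one after it in the same women. The schedule as written supplies only the second.

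Secondary objective 2 (section 2.1.2) asks whether fMRI is a sensitive way to study how gabapentin works. The ANOVA is the only stated comparison of the arms on the imaging data. Someone running section 9.2(iii) would have to improvise a different analysis. Someone running section 7.2 would never collect the data that section 9.2(iii) assumes. A pre-treatment scan cannot be recovered once a woman has started dosing. The pilot is also meant to inform the power of future fMRI studies, and one scan per woman gives no estimate of the pre/post correlation that a change design would need.

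**Working it through.** **The plan's own figure.** Section 9.1 gives 24 women for the imaging. It states no alpha, power, effect size or standard deviation, so no formula can reproduce the 24. The point is structural and does not depend on it.

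**Can the stated test be estimated?** Write the ANOVA as four columns: intercept, arm (0 placebo, 1 gabapentin), time (0 pre, 1 post) and arm × time.

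| Scan | Intercept | Arm | Time | Arm × time |
|---|---|---|---|---|
| Placebo, pre | 1 | 0 | 0 | 0 |
| Gabapentin, pre | 1 | 1 | 0 | 0 |
| Placebo, 3 months | 1 | 0 | 1 | 0 |
| Gabapentin, 3 months | 1 | 1 | 1 | 1 |

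- All four row types present (24 women × 2 scans = 48 scans): rank 4 of 4, and the interaction is estimable.
- Only the last two present (24 scans, as scheduled): the time column equals the intercept and arm × time equals arm. Rank is 2 of 4. Only the mean level and the between-arm difference at 3 months are estimable.

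The result is the same for any split of the 24 between the arms.

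**Could something else in the protocol serve as the pre measurement?**
- The alternating 16-second pain and rest blocks are a contrast within one scan, not before and after treatment.
- The step before the scan is a discomfort rating with no imaging.
- The healthy-volunteer scans, up to 4, are for calibration.
- Scanning at the same stage of the menstrual cycle sets when the scan falls and adds no second scan.

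**What the single scan can support.** Assumptions, none of them in the protocol: 1:1 split (12 per arm), two-sided test, 80% power. The normal approximation to the detectable standardised difference is (z for alpha/2 + z for power) × √(2/12), with √(2/12) = 0.408.
- Alpha 0.05: (1.960 + 0.842) × 0.408 = 1.14. The exact two-sample t solution is 1.20.
- Alpha 0.001: (3.291 + 0.842) × 0.408 = 1.69. The exact t solution is 1.93. The approximation is poor this far into the tail with 22 degrees of freedom.

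**What a pre-treatment scan would change.** Let r be the pre/post correlation, which the protocol does not give. At alpha 0.05 a change-score analysis detects 1.20 × √(2(1 − r)), and ANCOVA on the baseline scan detects 1.20 × √(1 − r²).

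| Assumed r | Change score | ANCOVA |
|---|---|---|
| 0.3 | 1.42 | 1.14 |
| 0.5 | 1.20 | 1.04 |
| 0.7 | 0.93 | 0.85 |
| 0.8 | 0.76 | 0.72 |

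The gain in sensitivity depends on r. At 0.5 or below, the change-score analysis does no better than the single scan.

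**The case against.** The strongest reply is that one named test fails, not the whole imaging analysis. That stands. A reader might infer that secondary objective 2 has no executable analysis, but the documents do not support this. The regression on behavioural measures can be run with one scan: the fMRI text collects a pain rating for this kind of analysis, and section 8 collects pain measures at 0 and 3 months. What the regression cannot do is show change in activation.

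A reader might also infer that a 3-month comparison of the arms is confounded by differences between women that existed before treatment. That does not follow either. Arms are randomised (section 5.5.1) and the Summary describes the imaging subset as random, so the comparison is unbiased in expectation. With about 12 per arm, chance imbalance and between-woman variance cost precision.

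It can further be said that the slip may lie in the schedule and not in the analysis text. The documents do not settle this. Section 7.2 refers to an appendix for more detail, and the flowcharts are not shown in the copy reviewed. A baseline scan drawn only there would contradict the Summary and section 7.2, so reconciliation would still be needed.

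Lastly, this is a pilot whose primary endpoints are recruitment and retention, and these are untouched. That limits the reach of the point but does not make the test runnable. Nor can the matter be left to a statistical analysis plan, which could change the model but could not supply a scan that was never scheduled.

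**Conclusion.** The contradiction is real. Section 9.2(iii) names a test that needs two scans per woman, and the text schedules one, on treatment. The time effect and the time-by-arm interaction cannot be estimated (rank 2 of 4). The only stated between-arm fMRI test cannot be run as written, and as the text stands 0 of 24 women have a scheduled pre-treatment scan. This rests on no numerical assumption, only on the written schedule, since the flowcharts could not be seen.

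The detectable differences of about 1.2 and 1.9 rest on an assumed 1:1 split, 80% power and the two alpha levels. They describe how sensitive a 3-month comparison would be. They should not be read as the cost of the missing scan, because that depends on a pre/post correlation the protocol does not give.

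**What to change.** Reconcile section 9.2(iii) with the scan schedule before the first woman in the imaging subset is dosed. There are two routes.

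**Keep the schedule as written.**
- Replace the ANOVA with a between-arm comparison of 3-month activation, with the participant as the unit of inference, adjusted for the 0-month pain score already collected.
- Regress 3-month activation on the 0-to-3-month change in pain score.
- Word the conclusion as a difference in activation at 3 months, not a change from pre-treatment.
- Align section 9.1 with this model. The 24 is justified there by fixed effect analyses, which does not match inference with the participant as the unit, so the number needs a new justification or a plain statement that it is pragmatic.

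The cost is a few sentences of protocol text and no new procedure. The price is a weaker, cross-sectional claim.

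**Keep the question of change.** The schedule would then have to include a pre-treatment scan for the subset, and the Summary, section 7.2 and the flowcharts would have to say so. The ANOVA becomes estimable, at the cost of an extra procedure for 24 women. The gain in precision is uncertain until the pre/post correlation is known.

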#### (iv) Pre-trial economic model and value of information analysis

In addition to data relating to the clinical and quality of life parameters, data on healthcare resource use will also be collected. A decision model will be developed to estimate the costs from the perspective of the NHS, and health outcomes in terms of quality

of life and quality adjusted life years associated with gabapentin and placebo based on the data from this pilot study and the literature. A probabilistic decision model will be constructed to simulate the clinical pathways associated with gabapentin and placebo, according to the guidance set out by NICE (NICE 2008). The basic model structure will consist of two arms, replicating the clinical consequences of patients receiving gabapentin and placebo. The main data source relating to the key parameters of the model will be provided by the pilot study. The mean costs and quality adjusted life years associated with both arms will be calculated for the modelling period (duration of the trial). Cost utility analysis will be carried out and incremental cost per quality-adjusted life years gained will be calculated. Particular consideration will be given to the potential for cost effectiveness to vary by particular patient characteristics or risk groups where suggested by the literature. Probability sensitivity analysis will be used to characterise uncertainty in parameters of the model, and presented using cost-effectiveness acceptability curves. Standard univariate sensitivity analysis will be carried out to explore areas of structural uncertainty in the analysis. Finally, a value of information analysis on the expected value of perfect information will also be carried out to quantify potential value of further research based on the difference between expected net benefit with perfect information and existing information.

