### 2.1.2 Secondary Objectives

1. To determine the effectiveness and acceptability to patients of the proposed methods of recruitment, randomisation, drug treatments, use of brain fMRI and follow-up
2. To determine whether fMRI of the brain a sensitive approach to determine the mechanism of action of gabapentin in the management of CPP
3. To determine whether gabapentin is likely to be cost effective given the current level of evidence and uncertainty, and to ascertain what further evidence is needed for the evaluation of gabapentin

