# 3 STUDY DESIGN

A two-arm parallel randomised controlled pilot trial. This will be a two centre pilot study with sites in NHS Lothian and NHS Grampian. We will recruit 60 patients over approximately nine months. After randomisation the participants will receive treatment for six months. Participants and the health care team will be unblinded at the end of their treatment.

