### 5.5 RANDOMISATION

#### 5.5.1 Randomisation Procedures

Eligible women will be randomised to either gabapentin or placebo using a web-based system. Women will be stratified by centre (Edinburgh and Aberdeen). We will use randomised blocks of varying sizes.

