## **8 DATA COLLECTION**

**Screening:** A member of the research team will carry out a screening visit to assess eligibility. All data will be recorded on a CRF and transferred to a secure database. Participants will be reminded to use effective contraception for the duration of the study and for one week after their last dose of gabapentin.

**Participant Log:** The clinical research team will keep an electronic log of women who fulfil the eligibility criteria, women who are invited to participate in the study, women recruited and women who leave the trial early. Reasons for non-recruitment (eg non-eligibility, refusal to participate, administrative error) will also be recorded. We will attempt to collect reasons for non-participation from women who decline to take part after previously providing contact details. During the course of the study, we will document reasons for withdrawal from the study and loss to follow-up.

**Treatment diaries:** details are documented in Section 6.5. All medications taken after screening and any medication other than the trial treatment taken during the study will be recorded in the treatment diary. This includes prescription and non-prescription treatment such as contraceptives, vitamins, topical preparations, herbal preparations and non-pharmacological therapies. Permissible and excluded concomitant medications are itemised. These restrictions apply during the period from screening to end of treatment. The permissible supplemental pain medications may be initiated at any time during the study (unless specified otherwise).

Questionnaires: A questionnaire will be given to all participants at randomisation (0 months) and at 3 months. This will include questions to capture the baseline demographic and clinical characteristics of the participants and include the following validated tools:

1. Neuropathic Pain Questionnaire (NPQ) (including Lickert pain score)
2. Brief Pain Inventory (BPI)
3. Pain Disability Questionnaire (PDQ)
4. Hospital Anxiety and Depression Score (HADS)
5. EQ5D QoL
6. WHO QoL
7. MYMOP patient-generated outcome questionnaire

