A further questionnaire will also be given to all participants at 6 months which will include the above and additional questions on whether they believed they were receiving Gabapentin or placebo, and also questions on acceptability of the allocation medication (and compliance) and on the acceptability of the above data collection methods. Lastly, we will ask the participants to complete a brief anonymous questionnaire once they have submitted their treatment diaries to assess level of adherence to diary keeping.

Focus groups: A purposive sample (based on age, social class and severity of symptoms) of 10 Edinburgh women (including some undergoing fMRI) and 10 Aberdeen women will be invited to participate in focus group discussions of the trial experience. Women who do not wish to participate in a focus group will be offered individual interviews using the same interview schedule. This will enable important issues arising in the focus groups to be explored in greater depth. Up to 20 interviews will be performed. Group/individual interviews will be audio-recorded, transcribed verbatim and analysed thematically to identify the issues of importance to participants.

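### Section 9.2(iv) builds the cost per QALY and the value-of-information result on mean QALYs by arm and makes no use of the baseline EQ-5D already collected, which costs precision at about 30 women per arm

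*Protocol*

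**What the plan says.** The economic work serves the third secondary objective in section 2.1.2: "To determine whether gabapentin is likely to be cost effective given the current level of evidence and uncertainty", together with what further evidence is needed. Section 9.2(iv) describes a probabilistic two-arm decision model whose key parameters come chiefly from the pilot, with literature as a further source. On the outcome it says: "The mean costs and quality adjusted life years associated with both arms will be calculated for the modelling period (duration of the trial", and then: "Cost utility analysis will be carried out and incremental cost per quality-adjusted life years gained will be calculated". Acceptability curves and an EVPI analysis complete the plan.

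EQ-5D is one of the instruments listed in section 8. On timing: "A questionnaire will be given to all participants at randomisation (0 months) and at 3 months", and "A further questionnaire will also be given to all participants at 6 months which will include the above". Utility is therefore available at 0, 3 and 6 months.

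On size and balance, section 3 says "We will recruit 60 patients over approximately nine months" and calls the design "A two-arm parallel randomised controlled pilot trial". Section 5.5.1 says "Women will be stratified by centre (Edinburgh and Aberdeen". No other stratification factor is named. The protocol neither provides for baseline adjustment of QALYs nor rules it out.

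**The concern.** If QALYs are formed as the area under the EQ-5D curve, the baseline value enters each woman's 6-month QALY directly and also predicts her later values. A simple difference in arm means then carries whatever baseline utility gap chance has produced, and the design does nothing to limit that gap. With about 30 women per arm it need not be small.

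At stake is the answer to the third secondary objective. The incremental QALY and its uncertainty drive the acceptability curve and the EVPI, and the EVPI is the figure meant to say how much further research is worth. A standard error larger than the collected data warrant makes that figure larger on average.

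**Working it through.** **The plan's own figure.** Section 9.2(iv) states no number. The only computed figure behind the 60 women is in section 9.1: a 95% CI of 11% to 32% for 12/60. The exact (Clopper-Pearson) interval is 10.8% to 32.3%, so that figure reproduces. It concerns loss to follow-up, not QALYs.

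**Inputs from the protocol.** 60 women, two arms, EQ-5D at 0, 3 and 6 months, horizon equal to the trial (6 months of treatment).

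**Assumptions, not in the protocol.** 1:1 allocation (30 per arm); QALYs from EQ-5D by the trapezoid rule; utility SD 0.20 to 0.30 at each visit; equal correlation r of 0.3 to 0.7 between visits. For EVPI: £20,000 per QALY and a known incremental cost of £0 or £200.

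**Formulas.**
- QALY: Q = 0.125·u0 + 0.25·u3 + 0.125·u6
- Var(Q) = (0.09375 + 0.15625·r)·SD²
- Slope of Q on u0: b = 0.125 + 0.375·r
- Share of variance explained: R² = b² / (0.09375 + 0.15625·r)
- Unadjusted SE = √(2·Var(Q)/30); adjusted SE = unadjusted SE × √(1 − R²). This is the large-sample form and ignores the small cost of estimating the extra coefficients.
- SE of the chance baseline gap = SD·√(2/30); shift from a one-SE gap = b × that SE

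**Worked case, r = 0.5, SD 0.25.** Var(Q) = 0.1719·SD²; b = 0.3125; R² = 0.3125²/0.1719 = 0.57. Unadjusted SE = 0.25·√(0.1719 × 2/30) = 0.0268. Adjusted SE = 0.0268·√(1 − 0.568) = 0.0176. Baseline gap SE = 0.25·√(2/30) = 0.065, so a one-SE gap moves the unadjusted incremental QALY by 0.3125 × 0.0645 = 0.0202.

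| r (SD 0.25, 30 per arm) | R² | Unadjusted SE | Adjusted SE | Ratio | Shift from a one-SE gap |
|---|---|---|---|---|---|
| 0.3 | 0.40 | 0.0242 | 0.0187 | 1.29 | 0.0153 |
| 0.5 | 0.57 | 0.0268 | 0.0176 | 1.52 | 0.0202 |
| 0.7 | 0.74 | 0.0291 | 0.0149 | 1.96 | 0.0250 |

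The ratio depends on r only. Over SD 0.20 to 0.30 the unadjusted SE runs from 0.019 to 0.035, the adjusted SE from 0.012 to 0.023, and the one-SE shift from 0.012 to 0.030. At r = 0.5 the unadjusted analysis of 30 per arm is about as precise as an adjusted one of 30 × (1 − 0.568) = 13 per arm.

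The shift is not an extra harm on top of the larger SE; it is the component that makes it larger: 0.0202² + 0.0176² = 0.0268².

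**With 20% loss (24 per arm).** The ratios are unchanged. At r = 0.5 and SD 0.25 the SEs are 0.0299 and 0.0197.

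**EVPI.** With incremental net benefit normal with mean m and SE s, EVPI per patient = s·φ(m/s) − |m|·Φ(−|m|/s). At m = 0 and SD 0.25:

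| r | Unadjusted | Adjusted |
|---|---|---|
| 0.3 | £193 | £149 |
| 0.5 | £214 | £140 |
| 0.7 | £232 | £119 |

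In simulations of 200,000 trials per scenario (SD 0.25, 30 per arm, true QALY gain 0 to 0.05), mean EVPI was higher without adjustment in every scenario; for example £89 against £58 at r = 0.5 with no true gain and no incremental cost. In single trials the unadjusted EVPI was the higher one in 62% to 97% of runs, depending on the scenario.

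**The case against.** The strongest reply is that the protocol is silent on adjustment and so has not chosen against it. Regression-adjusted means are still arm means, and covariates for a secondary economic outcome are often left to an analysis plan, which is not shown here. This stands to the extent that a reader might infer that 9.2(iv) prescribes unadjusted means; the text does not say so. What remains is that 9.2(iv) names the quantity and leaves the collected baseline out of it, so a literal reading yields unadjusted means.

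Second, the arms in that sentence may be those of the decision model, which also draws on literature. A pathway model could start both arms from a common baseline, and the protocol names neither EQ-5D as the QALY source nor an area-under-the-curve method. The effect may therefore be diluted. It is unlikely to vanish while the pilot is the principal source.

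Three stronger readings are tempting and are not supported:
- That the incremental QALY is biased. Over randomisations the unadjusted difference is unbiased. It is off only conditional on the gap actually observed, and its own SE already includes that variation.
- That a chance baseline gap always inflates the EVPI. A gap that moves net benefit away from zero lowers it; in 3% to 38% of simulated trials the unadjusted EVPI was the smaller.
- That the trial loses power on QALYs. Section 9.2(iv) plans no significance test of QALYs, so power is beside the point.

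**Conclusion.** The point holds as an avoidable loss of precision in a secondary analysis, not as an error in a stated number. Under the stated assumptions, leaving baseline utility out makes the SE of the pilot-derived incremental QALY about 1.3 to 2.0 times what the same data allow. The estimate is then sensitive to the observed baseline gap, and EVPI is overstated on average.

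The direction needs only that baseline utility correlates with the QALY, which is expected when baseline is a component of it. The size rests on an assumed SD, correlation, allocation ratio and QALY formula, none of which the protocol gives. Recruitment and retention, the primary endpoints of this pilot, are not touched.

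**What to change.** Add to section 9.2(iv): *The pilot-derived incremental QALY will be estimated by regression of each woman's QALY on treatment arm, baseline EQ-5D utility and centre. The adjusted difference and its standard error will enter the probabilistic model and the value of information analysis. Unadjusted means by arm will be shown alongside.* This wording also settles that EQ-5D is the source of the QALYs.

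The cost is one or two degrees of freedom and a rule for any missing baseline EQ-5D. If an analysis plan already specifies this adjustment, a cross-reference in 9.2(iv) is enough.

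### Objective 3 asks what further evidence is needed, but the only value-of-information measure in 9.2(iv) is overall EVPI, which cannot show which parameters need better evidence

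*Protocol*

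**What the plan says.** Section 2.1.2 of the protocol gives objective 3 two parts. The first is "To determine whether gabapentin is likely to be cost effective given the current level of evidence and uncertainty". The second is "to ascertain what further evidence is needed for the evaluation of gabapentin".

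Section 9.2(iv) describes the analysis that serves both parts. It plans a probabilistic decision model comparing gabapentin with placebo ("The basic model structure will consist of two arms"), "based on the data from this pilot study and the literature", over the length of the trial. It then plans a cost-utility analysis, a probabilistic sensitivity analysis shown as acceptability curves, a univariate sensitivity analysis directed at structural uncertainty, and attention to variation in cost-effectiveness between types of patient. The last step is "a value of information analysis on the expected value of perfect information will also be carried out to quantify potential value of further research", and the measure is defined as "based on the difference between expected net benefit with perfect information and existing information".

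No parameter or group of parameters is singled out in that definition, so it is the overall form of EVPI. The protocol mentions neither partial EVPI nor the expected value of sample information. It gives no willingness-to-pay threshold, beneficiary population or decision horizon for the value-of-information step.

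**The concern.** Overall EVPI answers one question: what is the most that resolving every uncertainty in the model could be worth? Objective 3 asks a different one: which evidence is missing? A single aggregate over all parameters cannot separate a model that is uncertain because the quality-of-life effect is poorly known from one that is uncertain because resource use, adherence or drug cost is poorly known. Those situations call for different data in the next study.

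The summary says the pilot exists to inform the planning of a future RCT. If the economic work reports only overall EVPI, the RCT team learns the ceiling on the value of research. It does not learn whether to spend effort on utilities, on resource-use capture or on discontinuation. The second half of objective 3 would then have no matching result.

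**Working it through.** **1. Does another planned analysis fill the gap?** Taking the components of 9.2(iv) in turn:

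- Cost-utility analysis and acceptability curves give the expected result and the probability of cost-effectiveness. That is the first half of objective 3. Neither attributes decision uncertainty to a parameter.
- The univariate sensitivity analysis is assigned to structural uncertainty. Even if applied to parameters, it would show how results move and not what resolving a parameter is worth.
- Variation by patient characteristics concerns heterogeneity between women, not uncertainty about a parameter's value.
- EVPI as defined resolves all parameters together.

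None of the four identifies which evidence is needed.

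**2. Can overall EVPI tell different situations apart?** The protocol states no EVPI, threshold or standard deviation, so there is no figure of its own to reproduce here. The following is an illustration.

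*Inputs.* Two options and 60 women, taken as 30 per arm (protocol; equal split assumed). Assumed, not in the documents: £20,000 per QALY, 6-month QALY SD 0.12, mean incremental net benefit m = £200, and a normal distribution with independent QALY and cost components. The assumed QALY SD alone gives a standard error of 20,000 × 0.12 × √(2/30) ≈ £620. I hold the total s at £620 and vary only how it is split.

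*Formula.* For two options, EVPI = s × [φ(d) − d × (1 − Φ(d))], with d = |m|/s.

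*Overall.* d = 200/620 = 0.3226, φ(d) = 0.3787 and 1 − Φ(d) = 0.3735. So EVPI = 620 × (0.3787 − 0.3226 × 0.3735) ≈ £160 per woman. A Monte Carlo check with 4 million draws gave £159.8.

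*Partial.* Use the same formula with s × √share for QALYs and s × √(1 − share) for costs. For a 5% QALY share, s = 620 × √0.05 = 138.6 and d = 1.443. The partial value is 138.6 × (0.1409 − 1.443 × 0.0746) ≈ £5.

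| QALY share of variance | Overall EVPI | Partial, QALYs | Partial, costs |
|---|---|---|---|
| 5% | £160 | £5 | £154 |
| 50% | £160 | £93 | £93 |
| 95% | £160 | £154 | £5 |

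The planned measure is the same in all three rows. The partial values point to three different priorities for further data.

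**3. How far to trust the illustration.** The rows show what the measure can and cannot distinguish; they do not forecast this trial. With QALY SD 0.08 to 0.16 and cost SD £300 to £1,000, the pilot's sampling error alone would put between 72% and 99% of the variance on QALYs. The extremes are 1,600²/(1,600² + 1,000²) = 0.72 and 3,200²/(3,200² + 300²) = 0.99. The 5% row is therefore an extreme case on these inputs. The conclusion does not depend on it, because overall EVPI is blind to the split whatever the split is.

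**The case against.** The strongest reply is that this is detail for a health-economics analysis plan. Section 9.2(iv) commits to a value-of-information analysis and does not say that only overall EVPI will be reported. Partial values come from the same simulation, and an unseen plan may include them. EVPI could also be shown across a range of thresholds instead of as one number. Part of this stands: nothing in 9.2(iv) is miscalculated, and the omission may already be repaired elsewhere. It does not dispose of the point, because the protocol is not silent. It selects a measure, defines it in a form that cannot serve half of its own objective, and gives that half no other analysis.

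It is also fair to say that EVPI is used correctly for the task 9.2(iv) gives it. It bounds the potential value of further research, and an EVPI below the cost of research can legitimately rule research out.

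A reader might go further and infer that EVPI will be large after almost any small pilot, and so will favour an RCT whatever is found, since "The main data source relating to the key parameters of the model will be provided by the pilot study". The documents do not support that:

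- EVPI is never negative, but it falls from 0.399s at zero mean net benefit to 0.083s at one standard error and 0.0085s at two.
- Simulated pilots (27 per arm, QALY SD 0.08 to 0.15, cost SD £500, gabapentin £100 dearer, £20,000 to £30,000 per QALY, 100,000 women, £2 million research cost, all assumed) put population EVPI above that cost in 80–92% of cases at a true gain of zero. At a gain of 0.10 QALY the range is 0.2–27%.
- The literature also feeds the model. The prevalence in section 1.1 is for all chronic pelvic pain, whereas the trial admits only women without obvious pathology at laparoscopy.
- The protocol states no rule for launching an RCT on the strength of EVPI.

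**Conclusion.** The point holds as a mismatch between an objective and its analysis. The second half of objective 3 has no analysis in 9.2(iv) able to answer it, because overall EVPI does not attribute decision uncertainty to parameters and no other listed component does. This follows from the definition in the protocol and needs no outside figures. The size shown, £160 overall against partial values of £5 to £154, is illustrative and rests on the assumed threshold, SD, mean net benefit, normality and independence.

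The weight is moderate. It affects one secondary objective of a pilot whose primary aim is recruitment and retention, but it bears on what the pilot can tell the designers of the RCT. It is not a finding that EVPI is invalid, or that it is biased towards recommending more research.

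**What to change.** In 9.2(iv), add the expected value of partial perfect information by parameter group: EQ-5D/QALY effect, healthcare resource use, adherence and discontinuation, and drug cost. Compute it from the probabilistic sensitivity analysis draws already planned. Say that these values will be used to answer the second half of objective 3, and that overall EVPI will be reported as an upper bound on the value of further research. State the threshold, beneficiary population and horizon used, since the scale of every value-of-information figure depends on them.

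The expected value of sample information is optional. It is needed only if the economic model will be used to justify or size the RCT, in which case it should be set against the cost of that trial.

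The cost is modest extra health-economics analysis time. No new data are needed: EQ-5D, resource use and compliance are already collected in the questionnaires and diaries (6.5, 8 and 9.2(ii)), and drug cost is an input the model needs in any case.
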